#### Inclusion criteria

2.3.4.

The inclusion criteria are as follows:
a.Gestational age at birth between 32 and 42 weeks.b.Respiratory disorders (tachypnea and expiratory grunting) lasting longer than 15 min after birth, present for at least 15 min in the first 6 h of life, or a need for noninvasive respiratory support between birth and 6 h of life.c.Available chest radiography obtained within 6 h after birth.d.Available parameters of the acid–base balance (blood pH, partial pressure of O_2_ and CO_2_, and base excess) and blood serum ionogram for Na^+^, K^+^, and Ca^2+^ evaluated in the umbilical cord blood sample.

#### Exclusion criteria

2.3.5.

The exclusion criteria are as follows:
a.Need for intubation directly after birth or perinatal asphyxia, defined as the abnormal acid–base parameters detected in an umbilical cord blood sample (pH < 7.0 or base excess ≤14 mmol/L).b.Multiple apnea-brady that require immediate intubation prior to an NIV trialc.Age > 24 h.d.Meconium aspiration syndrome.e.Air leak syndrome.f.Congenital heart disease.g.Congenital diaphragmatic hernia.h.Other severe congenital malformations and genetic disorders (diagnosed before and after birth) associated with an increased risk of respiratory failure.i.The need for surfactant administration immediately after birth, regardless of the method of administration (respiratory distress syndrome—RDS).

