**Methods and analysis:**

This multicenter, double-blind, phase III trial will include infants with a gestational age between 32 and 42 weeks who are affected by respiratory disorders and treated in eight neonatal intensive care units in Poland. A total of 608 infants within 24 h after birth will be enrolled and randomly assigned (1:1) to receive nebulized salbutamol with NIV or placebo (nebulized 0.9% NaCl) with NIV. The primary outcome is the percentage of infants with TTN who develop PPHN. The secondary outcomes are the severity of respiratory distress (assessed with the modified TTN Silverman score), frequency of need for intubation, duration of NIV and hospitalization, acid–base balance (blood pH, partial pressure of O_2_ and CO_2_, and base excess), and blood serum ionogram for Na^+^, K^+^, and Ca^2+^.

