### Secondary outcomes

2.7.

The secondary outcomes are the severity of respiratory distress (assessed with the modified TTN Silverman score, presented in Table 1) (32, 33), frequency of need for intubation, duration of NIV, duration of hospitalization, and blood levels of acid–base parameters [pH, partial pressure of CO_2_ (pCO_2_), partial pressure of O_2_, and base excess/deficit] and ions (sodium, potassium, and calcium).

**Table 1 T1:** Modified TTN Silverman score.

	0	1	2
Saturation^a^	>95%	90%–95%	<90%
Intercostal retraction	None	Mild	Continuous
Tachypnea	None	Mild	Continuous
Nasal flaring	None	Mild	Continuous
Expiratory grunting	None	Intermittent	Continuous

TTN, transient tachypnea of the newborn.

^a^
Measurement of post-ductal saturation during oxygen therapy.

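### As printed, the unsigned base-excess limit in the asphyxia exclusion is met by infants with normal values, contradicting its own purpose and the planned enrolment

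*Protocol article*

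**What the plan says.** Item a of section 2.3.5 (Exclusion criteria) excludes infants with "perinatal asphyxia, defined as the abnormal acid–base parameters detected in an umbilical cord blood sample", and gives the limits in brackets as "pH < 7.0 or base excess ≤14 mmol/L". In the second limit, "base excess ≤14 mmol/L", no minus sign is printed and the term is base excess rather than base deficit. Either limit is sufficient.

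Item d of section 2.3.4 (Inclusion criteria) requires "Available parameters of the acid–base balance (blood pH, partial pressure of O_2_ and CO_2_, and base excess" together with serum ions, all "evaluated in the umbilical cord blood sample". Every candidate therefore has a cord base-excess value to which the exclusion applies.

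No other section repeats the threshold or gives it with a sign. Section 2.7 (Secondary outcomes) uses a two-sided term for the same measurement, "partial pressure of O_2_, and base excess/deficit". On recruitment, the abstract states: "A total of 608 infants within 24 h after birth will be enrolled".

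**The concern.** A base excess of 0 is less than 14, and so is any negative value. Taken literally, the limit covers infants without acidosis as well as infants with it. The criterion is meant to separate asphyxiated infants from the rest. As printed it separates almost nobody, and the or makes the pH limit irrelevant for anyone whom the base-excess limit already catches.

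What is at stake is whether a numerical eligibility threshold in a phase III trial can be applied as written. A reader cannot tell from the article which infants this limit was meant to exclude, and anyone reproducing the population from it would have to guess.

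**Working it through.** The article gives no figure to reproduce here. The check is one of logic, followed by an illustration of size.

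**Step 1: the printed rule (section 2.3.5, item a).** Exclude if pH < 7.0 or BE ≤ 14, where BE is cord base excess in mmol/L. For BE = 0, 0 ≤ 14 is true, so the infant is excluded whatever the pH. The same holds for BE = −3 or BE = +2. Only infants with BE above +14 escape this limit.

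**Step 2: read the term as base deficit instead.** Deficit = −BE, so deficit ≤ 14 is the same as BE ≥ −14. An infant with BE = 0 has deficit 0 and is still excluded. An infant with BE = −20 has deficit 20 and is not excluded by this limit. The rule would remove infants without acidosis and keep the most acidotic, unless their pH were below 7.0. So either the sign is wrong, or the term and the direction of the inequality are both wrong.

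**Step 3: size of the literal reading.** The documents give no distribution, so I assume that BE is normal with mean μ from −8 to +2 and SD σ from 2 to 5 mmol/L. The share excluded by the printed limit is Φ((14 − μ)/σ).

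| μ | σ | (14 − μ)/σ | Share with BE ≤ 14 |
|---|---|---|---|
| −8 | 5 | 4.4 | 99.9995% |
| −4 | 4 | 4.5 | 99.9997% |
| −4 | 5 | 3.6 | 99.98% |
| 0 | 5 | 2.8 | 99.74% |
| +2 | 4 | 3.0 | 99.87% |
| +2 | 5 | 2.4 | 99.18% |

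The last row is the smallest share over the whole range. Even there, only 1 − 0.991802 = 0.0082 of infants pass this limit. Enrolling 608 would then mean screening about 608/0.0082 ≈ 74,000 infants, before any other criterion is applied.

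**Step 4: how much the sign matters.** With a minus sign in front of the printed number, the share excluded would be Φ((−14 − μ)/σ):

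- μ = −4, σ = 3: Φ(−3.33) = 0.04%
- μ = −4, σ = 4: Φ(−2.5) = 0.6%
- μ = −8, σ = 5: Φ(−1.2) = 11.5%, the largest in the range

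This shows only what one character does to the rule. It is not evidence that this signed value is the intended cut-off.

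**The case against.** The best reply is that this is a typographic slip that reveals itself. The sentence says that it is defining asphyxia, pairs the limit with a low pH, and sits in a plan to enrol 608 infants. No clinician would exclude an infant for a normal base excess. This stands, and it is why the practical effect is probably small.

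A second reply is that the minus sign may have been lost when the PDF was read. That is possible. The minus in the chloride symbol in the Introduction survives, but it is a superscript charge. The text has no other negative number in running type to test against, and the exponent in the pulmonary-pressure formula in section 2.8 was flattened. Loss in conversion is therefore neither shown nor excluded. A look at the full protocol settles it.

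Three stronger inferences are tempting, and the documents support none of them:

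- **Divergence between sites.** A reader might infer that the eight units would correct the rule in different ways and enrol different populations. The two obvious corrections, base excess ≤ −14 and base deficit ≥ 14, are the same rule and select the same infants.
- **A changed event rate.** The Introduction lists birth asphyxia among the causes of PPHN, so a reader might infer that the slip alters the PPHN incidence. Nothing in the article allows that change to be estimated. The criterion uses cord blood, so it acts before randomization and equally in both arms. The pH and intubation conditions also exclude some severe cases on their own.
- **An edit check that rejects everyone.** Nothing shows that the electronic case report form was programmed from this article. The registration statement cites protocol version 5.0, and section 2.10.1 places the data checks in a separate validation plan. Neither is shown. Recruitment was planned from December 31, 2021, and the article appeared on 2023-01-12. A check that rejected every infant would have been noticed at once.

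**Conclusion.** The point holds as an error in a stated eligibility threshold. The base-excess limit as printed captures normal values, and so contradicts both the purpose given in the same sentence and the planned enrolment of 608. Reading it as base deficit does not repair it.

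The logical contradiction needs no assumption beyond the meaning of base excess. The figure of more than 99% excluded rests on the assumed normal distribution and its range of means and SDs, and it holds at every combination tried.

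The consequence is limited. It is a wrong criterion in the published text that is cheap to correct. It is not evidence that the wrong infants were enrolled, that sites differed, or that the comparison of the arms is biased. Nor do the documents establish what the cut-off should be.

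**What to change.** 1. Compare item a of section 2.3.5 with protocol version 5.0. If the two differ, correct the article. If version 5.0 carries the same wording, correct it there as well.
2. Restate the criterion so that the term (excess or deficit), the sign and the direction of the inequality can be read only one way. The sponsor must take the value from its own source, because the article cannot supply it.
3. Confirm that the eligibility check in the electronic case report form uses the reconciled version, and that infants already enrolled were screened against it. Cord base excess is required at inclusion, so this needs no new data.

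The cost is a correction of a few characters, a look at one programmed rule, and one listing of cord base excess for enrolled infants. The sample size, randomization and analysis do not change.

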#### Early-onset infection/pneumonia procedure

2.3.6.

Diagnostics of early-onset infection/pneumonia follows the protocol in force. As the diagnosis of early-onset infection/pneumonia can be made later than in the first 6 h of the infant's life, patients with an infection (diagnosed on the basis a positive blood culture) or pneumonia (diagnosed on the basis of a chest x-ray) included in the study will be analysed as a separate subgroup.

#### Blinded (masking)

2.3.7.

The study team was divide between the blinded and non-blinded group. Members of the unblinded study team prepare the medicinal product/placebo (pharmacist). The remaining team members (doctors and nurses) and patiens and parents form the blinded study team.

### Procedures and interventions

2.4.

Enrolment will take place within and up to 24 h from birth (usually within the first 6 h of life). During enrolment, patients will be screened for the inclusion and exclusion criteria. Demographic data (including date and time of birth, sex, gestational age in weeks and days, and body weight at birth), obstetric history [type of delivery, single/multiple pregnancy, and prenatal steroid treatment (number of doses and date of last dose administered)], and Apgar scores will be collected, and physical examination will be conducted.

Researchers can use a variety of CPAP or NIV devices or modes, e.g., DuoPAP on FABIAN® (ACUTRONIC Medical Systems AG, Switzerland), CMV on Babylog® VN500 (Drägerwerk AG Co., Germany). Based on the available literature, it is not possible to clearly demonstrate the advantage of one of the modes of respiratory support over another in the treatment of respiratory failure in newborns. We would like the study to determine whether this is indeed the case and to what extent the change in the mode of non-invasive ventilation impacts the incidence of PPHN. Proposed CPAP initial settings: PEEP at 5–6 cm H_2_O pressure with an oxygen concentration of ≥21% to maintain pre-ductal saturation between 90% and 95%.

Patients assigned to the study group will be treated with 0.15 mg/kg body weight (diluted in 3 ml 0.9% NaCl) nebulized salbutamol (Ventolin®, GlaxoSmithKline, Dublin, Ireland) for 30 min. This dose was selected according to a previous study on salbutamol in TTN (31). The placebo group will be administered 3 ml nebulized 0.9% NaCl for 30 min.

The intervention period (during which patients will receive salbutamol or 0.9% NaCl together with NIV) will be divided into period I up to 24 h after enrolment and period II between 24 and 48 h after enrolment. Patients can be treated for up to 48 h from enrolment, with a maximum of four doses administered every 6 h. The extended follow-up period is planned between 48 h after enrolment and 7 days of life (or hospital discharge, whichever occurs first). The study design and planned examinations are shown in Figure 1.

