#### Computational methods

2.3.3.

Descriptive statistics for categorical variables will be presented as numbers, percentages, and relative frequencies, and that for continuous variables as means, standard deviations, medians, ranges, and interquartile ranges. The incidence of PPHN (primary outcome) between the salbutamol and placebo groups will be compared using the chi-square or Fisher's exact test (dependent on observed incidence). Potential determinants of PPHN will be analyzed using a logistic regression method. The secondary endpoint TTN scale will be analyzed using the Mann-Whitney test. Other exploratory analyses will be conducted using the Student's or Mann-Whitney *U* tests for continuous variables and the chi-square or Fisher's exact tests for categorical variables. Multivariate analyses will be conducted using linear or logistic regression methods. The normality of the distribution of the analyzed variables will be assessed using the Shapiro-Wilk test. Further, analyses will be performed using R 4.0.2 (or later) statistical software [R Core Team (2021). R: A language and environment for statistical computing. R Foundation for Statistical Computing, Vienna, Austria. URL: https://www.R-project.org/]. In all analyses, *α *= 0.05 will be set as the level of significance.

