### Participants timeline

2.5.

T_0_—screening and enrolment (birth to 24 h of life).T_0_—allocation and randomization (6 to 24 h of life).T_1_—first observation period (from randomization to 24 h after randomization).T_2_—second observation period (from 24 to 48 h after randomization).T_3_—extended observation period (from 48 h after randomization to discharge or 7 days of life, depending on which comes first).

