#### Evaluation of TTN

2.8.2.

The modified TTN Silverman score (32, 33) (Table 1) will be used to assess the severity of the respiratory disorder. The sum of the points will correspond to the Silverman score (0–10 range; the higher the score, the more severe the respiratory distress).

Based on Szymanski et al.'s study (13) on the evaluation of TTN, we propose to use a modified LUS score in neonates with respiratory distress, which includes posterior instead of lateral lung fields, and a five-grade rating scale, where “0” corresponded to normal lung and “4” indicated the presence of pulmonary consolidations (13). The sum of all four area scores will be the total LUS score, which will range from 0 to 16.

For NIV, the following information will be collected: start time, total duration in days, initial/maximal pressure, and initial/maximal FiO_2_.

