### Early termination

2.9.

A patient can be withdrawn from the study at any stage following the decision of the principal investigator or withdrawal of consent from the parent/legal guardian. Early termination can also occur in the following cases:
•An adverse event (AE) likely related to the treatment intervention.•The need for surfactant administration.The need for intubation or rapid worsening of respiratory function, which is defined as follows:
a.An increase in oxygen demand by >50% for >30 min or an increase in pCO_2_ above 70 mmHg in two consecutive examinations of blood acid–base parameters performed at a 1-h interval.b.Repeated (more than twice in 1 h) incidents of apnea lasting >20 s, defined as cessation of breathing and bradycardia <100 beats per minute with oxygen saturation <80%.c.The need for manual ventilation using a bag valve mask.•Improvement of respiratory function, allowing NIV discontinuation.•Severe violation of the eligibility criteria or study protocol.Early termination of participation in the study will result in the discontinuation of the treatment with salbutamol. After treatment discontinuation, the patient will be followed up according to the study protocol until the seventh day of life or hospital discharge.

In every case, the reason for withdrawal will be described in the electronic case report form. Patient data collected before the withdrawal can be included in the analysis by the sponsor.

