#### Safety monitoring

2.10.3.

Safety will be determined for all patients who receive salbutamol or placebo, according to the procedures described earlier in this section. Patients will be analyzed according to the actual treatment received. All data regarding safety from enrolment to the end of the follow-up period (seventh day of life or hospital discharge) will be reported and analyzed. AEs and serious AEs (SAEs) will be categorized according to the newest version of the MedDRA System Organ Class and Preferred Term classification. The severity of AEs and their relationship with treatment will also be reported.

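### Length of stay is a secondary outcome, but follow-up as written ends at day 7 of life; NIV time is listed only as a total in days

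*Protocol article*

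**What the plan says.** Secondary outcomes (2.7) lists "frequency of need for intubation, duration of NIV, duration of hospitalization" among the outcomes.

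Four sections put the end of observation at the same point:

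- Procedures and interventions (2.4): extended follow-up ends at "7 days of life (or hospital discharge, whichever occurs first".
- Participants timeline (2.5): the last period runs "from 48 h after randomization to discharge or 7 days of life, depending on which comes first".
- Early termination (2.9): after treatment is discontinued, "the patient will be followed up according to the study protocol until the seventh day of life or hospital discharge".
- Safety monitoring (2.10.3): safety data are reported "from enrolment to the end of the follow-up period (seventh day of life or hospital discharge".

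For NIV, Evaluation of TTN (2.8.2) lists the items to be collected, beginning with "start time, total duration in days, initial/maximal pressure". It mentions neither a stop time nor hours.

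For continuous variables, Computational methods (2.3.3) says "Other exploratory analyses will be conducted using the Student's or Mann-Whitney" tests, and names linear or logistic regression for multivariable work.

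**The concern.** Length of stay can be measured only if discharge is observed. An infant still in hospital at day 7 leaves the described observation window without a discharge date. Such infants are foreseeable: Randomization (2.3.1) has a separate stratum for 32+0 to 34+6 weeks, and infants whose treatment stops for intubation or rapid worsening keep the same day-7 limit.

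NIV time raises a related but smaller question. If the total is kept in whole days, infants supported for around a day fall into very few distinct values.

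Both outcomes matter to how the trial will be read. The Introduction cites shorter respiratory support and shorter hospital stay in an earlier study of 100 infants as evidence for salbutamol, and the Discussion lists shorter NIV among the expected short-term benefits. A later analysis plan can choose a method, but it cannot recover a discharge date or a stop time that was never recorded.

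**Working it through.** **The plan's own figures.** The article gives no expected stay, NIV time or effect size for either duration outcome, so there is no stated figure to reproduce. The only powered figure is 253 per group for PPHN (0.1% vs 4%). A two-sided, continuity-corrected two-proportion formula at 80% power gives 255 per group, so that figure reproduces within 1%. It bears on this point only as the group size used below.

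**Hospital stay cut at day 7.**

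Assumed inputs: stay X is lognormal with log-SD σ = 0.6; the true ratio of salbutamol to control is 0.85; there are 253 per group; the control median is set so that a chosen share exceeds 7 days.

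Formulas, with M = exp(μ + σ²/2) and a = (ln 7 − μ)/σ:

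- uncut mean: M
- mean cut at 7: M·Φ(a − σ) + 7·(1 − Φ(a))

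With 50% of controls beyond day 7, μ = ln 7:

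- Control, uncut: 7 × exp(0.18) = 8.38 days.
- Salbutamol, uncut: 0.85 × 8.38 = 7.12 days.
- Uncut difference: 1.26 days (average over 400 simulated trials: 1.24).
- Control, cut: a = 0, so 8.38 × 0.274 + 7 × 0.500 = 2.30 + 3.50 = 5.80 days.
- Salbutamol, cut: a = 0.1625/0.6 = 0.271, so 7.12 × 0.371 + 7 × 0.393 = 2.64 + 2.75 = 5.40 days (5.396 unrounded).
- Cut difference: 5.80 − 5.40 = 0.40 days (simulated: 0.40).

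Simulated results (400 trials per row, two-sided 0.05, cut and uncut tests run on the same data):

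| Controls beyond day 7 | Mean difference, uncut → cut (days) | Mann-Whitney power, uncut → cut | t-test power, uncut → cut |
|---|---|---|---|
| 10% | 0.58 → 0.47 | 87% → 87% | 80% → 86% |
| 25% | 0.82 → 0.49 | 84% → 83% | 78% → 82% |
| 50% | 1.24 → 0.40 | 82% → 80% | 77% → 79% |
| 75% | 1.81 → 0.23 | 82% → 63% | 77% → 60% |

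The reported difference in days shrinks throughout. Power is hardly touched until most infants stay past day 7. The t-test even gains a little at lower shares, because the cut also removes the long upper tail. So the main harm is to the estimate.

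**NIV in whole days instead of hours.**

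Assumed inputs: lognormal NIV time, log-SD 0.8, ratio 0.8, 253 per group, totals rounded up to whole days.

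| Control median | Mann-Whitney power, hours → whole days |
|---|---|
| 18 h | 84% → 67% |
| 24 h | 88% → 81% |
| 36 h | 91% → 87% |
| 48 h | 87% → 85% |

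With 400 trials, each power figure has a standard error of about 2 points: √(0.85 × 0.15/400) = 0.018. A rank test in hours does not depend on the median when the ratio is fixed, so the 84–91% spread is simulation noise. The loss within each row is what to read.

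**The case against.** **The article does not say that later discharge dates go unrecorded.** It defines an observation window. Data-collection details are left to a data management plan, and the full protocol or case report form may hold the actual discharge date. This stands: if the field exists, the text needs only a clarification. The conflict between outcome and window is still in the article as published.

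**Days need not mean whole days.** This also stands. Decimal days are not excluded, and for one continuous NIV spell a start time plus an exact total fixes the stop time. The 48 h limit applies to study drug, not to NIV. Days coarsen the record; they do not truncate it. NIV time is cut off only in infants still on NIV at day 7, a share not given.

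**A reader might infer that Mann-Whitney fails under the cut-off.** It does not. The limit is common to all infants, so cut stays become ties at the top rank and the test remains valid. In a check with assumed stratum medians of 21, 8 and 4 days (log-SD 0.4, ratio 0.88, stratum shares 30/35/35%), its type I error with the cut was 5.5% in 3,000 runs, and its power went from 44% to 40%. A test stratified by gestational age would lose more under those inputs, but the article names no such test.

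**A reader might infer that NIV time ends at intubation, so that failures count as short NIV.** The article has no such rule. Early termination lists "The need for intubation or rapid worsening of respiratory function" as a ground for stopping study treatment, and follow-up continues. How intubation or death enters NIV duration may properly be left to the analysis plan, and intubation is a secondary outcome in its own right. Replacing NIV duration by a ranked composite would be a choice of estimand, not a correction.

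**Conclusion.** The point holds in limited form. Duration of hospitalization and a follow-up window that closes at day 7 do not fit together. Followed literally, the trial would report stay up to day 7 rather than length of stay, with differences in mean stay (t-test, linear regression) compressed.

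Under the lognormal assumptions, about two thirds of the mean difference is lost when half the controls stay beyond day 7 (1 − 0.40/1.24 = 68%), with 2 points of Mann-Whitney power. At 75% the power loss is 19 points. The article gives no share beyond day 7, so the size for this trial is unknown.

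The NIV point is weaker. It matters only if whole days are recorded and NIV lasts roughly a day or less: 7 points of power at a 24 h median, 2 points at 48 h.

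Both are unpowered secondary outcomes, and the PPHN analysis is unaffected. The change is still worth making, because it concerns what is collected and cannot be put right at analysis.

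**What to change.** - Record the actual discharge date for every infant, including discharges after day 7, and say in 2.4 and 2.5 that this item is collected beyond the observation window. If the case report form already holds it, say so.
- Add the NIV stop date and time to the list in 2.8.2, and analyse NIV duration in hours.

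The cost is two fields taken from the hospital record, with no extra visits or examinations. The downside is that database close has to wait for the last discharge.
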